### Randomization, Allocation Concealment, and Blinding

Participants fulfilling eligibility criteria and willing to participate in this study will be randomly allocated to 1 of the 3 training conditions after the baseline assessment. Randomization will be performed before participants are enrolled by an independent person blinded to all processes within the intervention, using a computerized random number generator. A block randomization technique will be used, allowing 6 participants at a time to be randomized in equal proportions to the 3 training arms. The allocation numbers will be stored on a password-protected university database maintained by the same independent person and will be revealed after participants are enrolled and baseline assessments are completed.

Each time a participant completes the baseline survey, an automatic email will be sent to the principal researcher ([name]). After receiving this email, the participant will be allocated to the next number on the list and, consequently, be assigned to a training arm. Researchers and participants will be blinded to group allocation throughout the trial (ie, double-blind study design). Furthermore, as assessments and training will occur on the web, in the absence of the investigators, the outcome data will be blinded. However, it is possible that a researcher could become aware of the participants’ training conditions to support them adequately in the instance of technical problems. However, it is unlikely that this will entail problems of bias allocation or assessment because of the web-based nature of the study.

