#### Baseline Information

At baseline, participants will report on demographic information pertaining to age, gender, first language, country of birth, country of residence, postcode of current home address, ethnicity, marital status, employment status, education level, and hand preference. Participants will also report on the type of computer (eg, laptop), screen size and keyboard (eg, QWERTY) they are using, their health in general, whether they currently have a mental health condition (eg, depression), and on their pain experience information, including current pain problems, formal diagnosis of the pain condition (ie, by a physician), duration of primary pain condition, body locations where they experience pain, area of the body that hurts the most, how the primary pain condition began (eg, postsurgical), current treatment for the pain problem (eg, physiotherapy), and frequency of health care use.

To provide additional information characterizing participants’ overall pain severity, participants will complete the Graded Chronic Pain Scale (GCPS) [50]. The GCPS is a 7-item self-report instrument designed to assess 2 dimensions of chronic pain severity (pain intensity and pain-related disability) in the general population and in primary health care settings. The scale measures the presence of chronic pain in the past 6 months, and all items, except for the number of days disabled, are scored on an 11-point Likert scale, with responses ranging from 0 to 10. Subscale scores (ie, characteristic pain intensity, disability score, and disability points) for the 2 dimensions are combined to calculate a chronic pain grade that allows individuals with chronic pain to be classified into 1 of 5 hierarchical categories: grades 0 (*no pain problem*) to 4 (*high disability-high intensity*). The GCPS has been found to have acceptable to excellent internal consistency, with a Cronbach α ranging from .74 to .91 [50,51]. Dunn et al [52] found that the test–retest reliability after a 2-week interval was good, with a weighted Cohen κ of 0.81.

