### Statistical Methods

#### Overview

Statistical analyses will be conducted after data collection is completed using the SPSS version 27.0 or later (IBM Corp). Continuous data will be presented as means and SDs, whereas categorical data will be presented as frequencies and percentages. Analyses will follow the intention-to-treat principle and will include all randomized participants who successfully complete at least one training session (ie, minimum threshold exposure to ABMT). To determine whether there are any pretraining differences between the training conditions on demographic variables and baseline characteristics, a series of analyses will be performed. The rates of and reasons for missing data will be reported. To manage missing data, the study will attempt to follow-up on all randomized participants (even if they withdraw from the trial) and, where appropriate, use multilevel modeling for repeated measure data analyses as it allows the incorporation of all available data. Significance for all statistical tests will be set at *P*<.05 (2-tailed). Effect sizes will be presented by its most appropriate effect size (and 95% CI), as described by Lakens [82], with a preference for Cohen *d* where possible [83]. No interim analyses of the trial outcome data are planned.

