#### Engagement Measures

To examine changes in task-related engagement in different training conditions, a multilevel modeling analysis will be conducted. The time point (level 1 units) will be nested within participants (level 2 units). The variable time will have 6 levels (ie, after sessions 1, 2, 3, 4, 5, and 6). A model-building procedure [84] will be used to build the most parsimonious model to test the hypotheses, using the AIC to identify the most appropriate model. The model will be computed using maximum likelihood estimation. To analyze the impact of gamification on interest and enjoyment, a 1-way analysis of variance will be performed. Missing values will be handled using multiple imputations.

Regarding behavioral engagement, Kaplan-Meier survival curves [85] will be calculated to assess the time at which attrition occurred in each training condition and compared statistically using a log-rank test. Participants will be classified as noncompleters if they do not complete all 6 training sessions. Finally, a 1-way analysis of variance will be performed to determine whether there are differences in the mean number of sessions completed between the training conditions.

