#### Exploratory Analyses and Subgroup Analyses

Additional exploratory and subgroup analyses will be performed to explore the role of engagement metrics (ie, number of training sessions completed) and individual differences (ie, attentional control, pain-related worrying, personality characteristics, and recruitment setting [clinical vs nonclinical]) in the impact of training conditions on the primary outcomes. These analyses will be conducted using appropriate statistics and are subject to the final sample size and power.

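### Baseline significance tests between randomised arms are uninformative, and three of the four engagement analyses use no baseline covariate and may lose a little precision (low severity)

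*Protocol article*

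**What the plan says.** The protocol article (Statistical Methods, Overview) first provides for descriptive presentation: means and SDs, or frequencies and percentages. It then adds a separate step, meant to establish "whether there are any pretraining differences between the training conditions on demographic variables and baseline characteristics, a series of analyses will be performed". In the same paragraph it states that "Significance for all statistical tests will be set at" a two-sided P<.05. It does not say which variables or tests are meant, or what follows from a difference. Allocation is computer-generated in blocks, "allowing 6 participants at a time to be randomized in equal proportions to the 3 training arms", and no stratification factor is mentioned.

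The Engagement Measures section describes four analyses. For the first, "To analyze the impact of gamification on interest and enjoyment, a 1-way analysis of variance will be performed". Sessions completed are also compared by 1-way ANOVA, and attrition by Kaplan-Meier curves with a log-rank test. None of these three has a covariate. The fourth, the rating given after each session, uses a multilevel model built by AIC, for which covariates are neither listed nor excluded.

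The section on exploratory and subgroup analyses names "attentional control, pain-related worrying, personality characteristics, and recruitment setting" as individual differences to be explored in the effect of training on the primary outcomes.

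**The concern.** Among all participants randomised, a pretraining difference between arms arises by chance. A P value for it answers a question whose answer is already known. It also says nothing about the question that matters, which is whether the variable predicts the outcome strongly enough for the imbalance to move the estimate. A small significant imbalance on an irrelevant variable is harmless. A larger nonsignificant one on a strong predictor may not be. With many variables collected, a spurious difference is likely and would then need explaining.

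The engagement outcomes have no pretraining score, so unlike the symptom outcomes they have no built-in baseline adjustment. Several scales are already completed in the baseline survey before allocation, and recruitment route is known by then. If any of these predict engagement, the two ANOVAs and the log-rank test leave some precision unused. The sample size was set by reference to other studies and not by a power calculation for this trial, so inexpensive precision has some value.

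**Working it through.** The plan gives no figure of its own on this point, so there is none to reproduce.

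**1. How many variables could be tested.** This is a count of what is collected; the plan does not say that all of it is tested.
- Demographics (Baseline Information): "age, gender, first language, country of birth, country of residence, postcode of current home address, ethnicity, marital status, employment status, education level, and hand preference", which is 11.
- Equipment and health: computer type, screen size, keyboard, general health and current mental health condition, which is 5.
- Pain-experience questions: 8. Graded Chronic Pain Scale: 1.
- Subtotal: 11 + 5 + 8 + 1 = 25.
- Table 1 adds 6 outcomes with a baseline value (pain intensity, pain interference, attentional bias, anxiety, depression, interpretation bias) and 4 scales (ACS, BIS, BAS, PCS). Total: 25 + 10 = 35.

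**2. Chance findings at P<.05.** Assume that all null hypotheses are true. The expected number is 0.05k. If the tests are also independent, the chance of at least one is 1 − 0.95^k.
- k = 25: 1.25 expected; 1 − 0.95^25 = 72%.
- k = 30: 1.5 expected; 79%.
- k = 35: 1.75 expected; 83%.
- If only the 11 demographics were tested: 0.55 expected; 1 − 0.95^11 = 43%.

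The expected number does not need independence, but the probability does. Positive correlation among the pain and mood scales would lower it.

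**3. Is an unadjusted comparison invalid?** A simulation of 20,000 null trials with 3 × 40 participants and one covariate gave these rejection rates for the three-arm comparison:
- Covariate-outcome correlation 0.3: 5.3% unadjusted, 5.2% adjusted.
- Correlation 0.5: 4.8% unadjusted, 5.2% adjusted.

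Both hold the nominal 5%. Only within the subset of trials where the covariate itself differed at P<.05 did the unadjusted rate rise, to 9.8% and 15.0% respectively. The correlations are assumed.

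**4. Precision that adjustment could add to the ANOVAs.** The ratio of adjusted to unadjusted standard error is √(1 − R²), where R² is the share of outcome variance explained. The documents give no R².
- R² = 0.02: 0.990, so 1.0% smaller.
- R² = 0.05: 0.975, so 2.5% smaller.
- R² = 0.10: 0.949, so 5.1% smaller.
- R² = 0.20: 0.894, so 10.6% smaller.

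Power for one pairwise contrast is approximately Φ(d√(n/2)/√(1 − R²) − 1.96). For R² = 0, 0.05 and 0.20:
- n = 40 per arm, d = 0.72 (the pooled engagement effect cited in the Gamified ABMT section): 89.6, 91.0 and 95.0%.
- n = 40, d = 0.5 (assumed): 60.9, 63.1 and 70.5%.
- n = 28 (40 × 0.70), d = 0.5: 46.4, 48.4 and 55.2%. Allowing for four covariate degrees of freedom with the noncentral t, this becomes about 46% rising to 47 to 54%.

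The 28-per-arm case is pessimistic: sessions completed are known for dropouts, and interest and enjoyment is multiply imputed. The √(1 − R²) formula applies to the two ANOVAs. It does not carry over to the log-rank test.

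**5. Which primary outcomes are touched.** For pain intensity and pain interference, the pretraining value is one of the three time points in the multilevel model (Symptom Measures). They are outside this point.

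**The case against.** The strongest reply is that nothing here threatens a primary result. Unadjusted ANOVA and log-rank comparisons of randomised arms are valid, and their 5% error already allows for chance imbalance. Step 3 bears this out, and the reply stands. A reader might infer that imbalances bias the engagement comparisons; the documents do not support that.

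Four further inferences also go too far.
- That the plan ignores predictors of engagement it has itself named. The exploratory section names possible moderators of the training effect, which are not the same as prognostic covariates. They are candidates only.
- That no engagement outcome is adjusted. The session-rating model does not exclude covariates.
- That baseline differences will be reported as findings or used to pick covariates. The plan states no use for them.
- That every baseline null hypothesis is true by design. The analysis set keeps only participants who complete at least one session, a selection made after allocation. The Procedure section also places cognitive assessments in the first training session, after randomisation. A difference in that set, or on those measures, need not be pure chance. A P value does not settle that either.

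It can also be said that covariate lists belong in an analysis plan that is not shown. That is fair for the multilevel models. It has less force for the three analyses whose methods the article fixes as unadjusted. Finally, the word analyses might mean description only. But description is provided for separately, and the P<.05 rule covers all tests, so testing is the more natural reading.

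**Conclusion.** The point holds at low severity, in two parts of unequal strength.

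The firmer part is the baseline comparison. Significance tests there are uninformative, and a spurious difference is likely: 72 to 83% if 25 to 35 independent tests are run with true nulls, and less if fewer or correlated variables are tested.

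The weaker part is precision. Three of the four engagement analyses forgo baseline covariates. For the two ANOVAs, adjustment would shrink standard errors by 2.5 to 10.6% if R² is 5 to 20%, and by about 1% if R² is 2%. R² is an assumption throughout, so the gain may be very small. No bias, inflated overall error rate or effect on pain intensity or pain interference follows.

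**What to change.** - Delete the baseline significance tests and state that baseline data will be tabulated by arm. The descriptive statistics needed are already planned, so this costs nothing.
- For interest and enjoyment and for sessions completed, prespecify a small set of covariates known before allocation and use the ANCOVA form. Recruitment setting with one or more of the baseline ACS, PCS and BIS/BAS scores would serve. Fix the choice now, regardless of observed imbalance, and put the same covariates in the imputation model for interest and enjoyment. Measures taken in the first training session should not be treated as pre-allocation covariates.
- Optionally, report an adjusted time-to-attrition model beside the log-rank test.

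No new data are needed. With 120 analysed, three single-degree-of-freedom covariates would reduce the residual degrees of freedom from 120 − 3 = 117 to 114. The drawback is that the return may be small if the chosen covariates turn out to predict engagement weakly.

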#### Symptom Measures

To determine symptom changes (ie, pain intensity, pain interference, anxiety, and depression) in the different training conditions, multilevel modeling analyses will be conducted. For each model, the time point (level 1 units) will be nested within participants (level 2 units). The variable time for each symptom measure will have 3 levels (ie, pretraining, posttraining, and 1-month follow-up), with pretraining as the reference point. The control group (control ABMT) will serve as a reference group for comparisons between the groups over time. A model-building procedure [84] will be used to build the most parsimonious model to test the hypotheses, using the Akaike information criterion (AIC) to identify the most appropriate model. All models will be computed using maximum likelihood estimation.

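### Symptom models: no baseline adjustment is fixed, and on the conventional reading the treatment effects are change-from-baseline contrasts, unbiased but less precise than baseline-adjusted ones

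*Protocol article*

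**What the plan says.** The Symptom Measures section covers pain intensity and pain interference (primary) and anxiety and depression (secondary). It puts the pretraining score into the outcome of a multilevel model: "The variable time for each symptom measure will have 3 levels (ie, pretraining, posttraining, and 1-month follow-up), with pretraining as the reference point". On the group contrast it says: "The control group (control ABMT) will serve as a reference group for comparisons between the groups over time". The terms are not listed; they are to be chosen from the data: "A model-building procedure [84] will be used to build the most parsimonious model to test the hypotheses, using the Akaike information criterion (AIC"). The section names neither a baseline covariate nor a common pretraining mean across arms.

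Two other places bear on this. Under Randomization, Allocation Concealment, and Blinding, participants "will be randomly allocated to 1 of the 3 training conditions after the baseline assessment", so the pretraining score precedes allocation. The Statistical Methods overview limits the analysis set to randomised participants who finished one session or more. It also plans analyses of "whether there are any pretraining differences between the training conditions on demographic variables and baseline characteristics", but does not say that their results feed into the symptom models.

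**The concern.** With pretraining as the reference level of time, the usual group, time and group-by-time model gives each arm its own pretraining mean. Each treatment effect is then the difference between arms in change from that mean. Because allocation follows the baseline assessment, a pretraining difference among all randomised participants is chance. Subtracting the whole of it, rather than the part that predicts the later score, adds noise.

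The stake is power. The target is 40 per arm, dropout of about 30% is expected, and the Sample Size Estimation section says there is no earlier effect size to plan on. The hypotheses also need gamified against standard ABMT, not only each against sham. An avoidable loss of precision matters in a trial of this size.

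**Working it through.** The article states no correlation, precision or power for these models, so there is no figure of its own to reproduce.

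**Inputs from the article:** three time levels with pretraining as reference; control ABMT as reference group; baseline before allocation; 1:1:1 allocation in blocks of 6; two-sided 0.05; minimum 30 per arm; target 40 per arm; about 30% dropout, so 40 × 0.70 = 28 per arm at later visits. **Assumed:** rho, the correlation between the pretraining and later score, over 0.3 to 0.9; equal variances across visits.

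**Step 1: complete data.** With n per arm and SD s:

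- change contrast: variance = 2(1-rho) × 2s²/n
- baseline-adjusted contrast: variance = (1-rho²) × 2s²/n
- ratio = (1+rho)/2, so the loss of precision is 1-(1+rho)/2 = (1-rho)/2

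| rho | 2(1-rho) | 1-rho² | ratio | precision lost | fall in standard error after the fix |
|---|---|---|---|---|---|
| 0.3 | 1.40 | 0.91 | 0.65 | 35% | 19.4% |
| 0.5 | 1.00 | 0.75 | 0.75 | 25% | 13.4% |
| 0.7 | 0.60 | 0.51 | 0.85 | 15% | 7.8% |
| 0.9 | 0.20 | 0.19 | 0.95 | 5% | 2.5% |

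**Step 2: expected dropout.** Take 40 per arm at baseline and 28 at both later visits, under compound symmetry. Per arm, with s = 1, the free-baseline contrast has variance (1-rho²)/28 + (1-rho)²/40, and the adjusted one has (1-rho²)/28.

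- rho 0.5: 0.75/28 = 0.02679 and 0.25/40 = 0.00625; loss = 0.00625/0.03304 = 18.9%
- rho 0.6: 0.64/28 = 0.02286 and 0.16/40 = 0.00400; loss = 0.00400/0.02686 = 14.9%
- rho 0.7: 0.51/28 = 0.01821 and 0.09/40 = 0.00225; loss = 0.00225/0.02046 = 11.0%

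Inverting the generalised least squares information matrix for three arms and three visits gives the same three figures.

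**Step 3: correlation that decays with time.** Under AR(1) with complete data, the baseline to 1-month correlation is the square of the adjacent-visit one. At 0.5 it is 0.25 and the 1-month loss is (1-0.25)/2 = 37.5%; at 0.7 it is 0.49 and the loss is 25.5%.

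**Step 4: power, as illustration only.** With 30 per arm, complete data and an assumed between-arm effect of 0.45 SD, pairwise power rises from 41.4% to 52.1% at rho 0.5 and from 61.4% to 68.5% at rho 0.7.

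**Step 5: does AIC selection deliver the adjustment?** With group and time as categorical factors, removing the group main effect but keeping the full interaction only re-parameterises the same nine cell means (design rank 9 either way). A common pretraining mean has rank 7 and needs hand-coded group-by-post-baseline terms. If such terms were offered, AIC would keep the two extra baseline parameters whenever the likelihood-ratio statistic exceeded 4, which under equal baselines happens with probability P(chi-square on 2 df > 4) = 13.5%. The estimator would then depend on the chance imbalance observed.

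**The case against.** The strongest reply is that the model criticised is inferred. A reader might take the section to say that each arm has its own pretraining mean. It does not say so: a group main effect is neither stated nor excluded, and the time coding would also fit a common-baseline model. A journal article may leave exact terms to an analysis plan. This stands, and it is why the point is conditional on the conventional reading. But the article is not silent on the terms: it commits to choosing them by AIC, and Step 5 shows that this is no safeguard.

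A reader might also infer a fixed loss of 15-25%. That range needs rho between 0.5 and 0.7 and complete data, and the article supplies neither. The 0.45 SD in Step 4 is likewise an assumption: the article cites 0.45 as found in the intervention group of an earlier trial, not as its own planning effect.

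Nor is the planned contrast biased. A difference in change is unbiased under randomisation and fits hypotheses worded as reductions.

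Equal baseline means are guaranteed only among all randomised participants. The one-session rule selects after randomisation, and the Validity Check exclusion draws partly on posttraining answers. Forcing a common mean in that set is an assumption. This stands and decides the preferred form of the fix.

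Finally, two additions are tempting but weak. Dropping the baseline comparisons would change no treatment estimate. The article uses "recruitment setting [clinical vs nonclinical"] only in exploratory and subgroup analyses, and nothing in it shows how prognostic setting is.

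**Conclusion.** The concern holds as a conditional efficiency point. The article fixes no baseline adjustment for the four symptom outcomes, and on the conventional reading its treatment effects are less precise than they could be for any rho below 1. The loss in inverse variance runs from 35% (rho 0.3) to 5% (rho 0.9) with complete data. For rho 0.5-0.7 the expected dropout under compound symmetry reduces it to about 11-19%; a correlation that decays over time would make it larger at 1 month. These sizes rest on an assumed rho, equal variances and the retention of a group main effect or its equivalent. Validity is not in question.

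**What to change.** Prespecify, outside the AIC selection, that the posttraining and 1-month scores of pain intensity, pain interference, anxiety and depression are modelled with fixed effects for group, time (two levels), group-by-time, pretraining score and pretraining-score-by-time. This does not require exactly equal baseline means in the analysis set.

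If all randomised participants are included, an alternative is to keep pretraining in the outcome with one mean common to the three arms. The group-by-post-baseline terms must then be coded by hand, because removing the group main effect from a factorial specification does not impose the constraint.

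Recruitment setting may be added as an optional covariate, with its prognostic value stated as an assumption.

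The cost is a few lines of model specification. Table 1 already schedules all four scores at baseline, so no new data are needed. Under the covariate form, participants with no later score do not contribute. In the dropout scenario of Step 2 (equal dropout across arms) this loses no precision against the common-mean model.

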### Aims and Hypotheses

The aim of this study is to investigate the effects of a gamified web-delivered ABMT intervention in a sample of adults with chronic musculoskeletal pain via a randomized, double-blind, placebo-controlled trial. To do this, 3 ABMT conditions will be directly compared: nongamified sham control ABMT, nongamified standard ABMT, and gamified ABMT. It is hypothesized that the gamified ABMT condition, relative to both the standard ABMT and control ABMT conditions, will rate more highly on self-reported engagement (ie, task-related engagement, enjoyment, and interest) as well as complete more training sessions and have less dropout. On the basis of the findings from the broader ABMT literature and theoretical considerations [20-22], it is expected that the standard ABMT and gamified ABMT conditions will show a reduction in pain-related attentional biases and interpretation biases after training sessions, with the largest reduction in the gamified ABMT condition. Furthermore, it is expected that both the standard ABMT and gamified ABMT conditions, relative to the control ABMT condition, will show reductions in pain intensity, pain interference, anxiety, and depression scores immediately after training and 1-month later and that these reductions will be greater in the gamified ABMT condition compared with the standard ABMT condition. Finally, it is expected that both the standard ABMT and gamified ABMT conditions, relative to the control ABMT condition, will report global pain-related improvements following training and that these improvements will be larger in the gamified ABMT condition compared with the standard ABMT condition.

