### Strengths and Limitations

This study has significant strengths. First, findings from the 3-arm randomized controlled trial design, with the inclusion of a nongamified version of the intervention, will allow us to determine whether the addition of game elements leads to increased motivation, engagement, and intervention efficacy. Further strengths of the study include (1) the rigorous, well-designed, and prespecified study protocol that has been reported as per SPIRIT [23] guidelines and preregistered on a clinical trial registry; (2) the use of an empirically supported set of pain-relevant word stimuli; (3) the inclusion of self-report and behavioral measures of engagement as a primary outcome; (4) the large chronic pain sample drawn from clinical and nonclinical settings; and (5) the inclusion of a 1-month follow-up assessment.

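### Gamified versus standard ABMT is a stated hypothesis and the reason for the three-arm design, but no analysis specifies that comparison

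*Protocol article*

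**What the plan says.** The hypotheses in Aims and Hypotheses name the comparison repeatedly. The section announces that "3 ABMT conditions will be directly compared". On engagement, the gamified arm, "relative to both the standard ABMT and control ABMT conditions, will rate more highly on self-reported engagement". On pain intensity, pain interference, anxiety and depression, "these reductions will be greater in the gamified ABMT condition compared with the standard ABMT condition". The same ordering is predicted for attentional and interpretation bias and for global improvement. Strengths and Limitations gives the purpose of the nongamified active arm: the design "will allow us to determine whether the addition of game elements leads to increased motivation, engagement, and intervention efficacy".

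Statistical Methods then sets out these analyses:

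- **Symptom Measures:** a multilevel model, with "The control group (control ABMT) will serve as a reference group for comparisons between the groups over time". The same sentence stands under Cognitive Measures and Perceived Improvements.
- **Engagement Measures, task-related engagement:** a multilevel model over six sessions, with no reference group and no contrast named.
- **Engagement Measures, interest and enjoyment:** "To analyze the impact of gamification on interest and enjoyment, a 1-way analysis of variance will be performed".
- **Engagement Measures, behavioural engagement:** a log-rank test across conditions for attrition, and a one-way analysis of variance for sessions completed.

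All the multilevel models are chosen by AIC; for the symptom models the stated purpose is "to build the most parsimonious model to test the hypotheses".

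**The concern.** With sham as the reference category, the group-by-time coefficients that the software prints are standard versus sham and gamified versus sham. Neither isolates the game. The gamified task is described as a shell laid over the unchanged standard task, so gamified and standard differ in game elements only. Gamified and sham differ in game elements and also in probe contingency (87.5% of probes at the neutral word, against 50%).

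The overall tests for enjoyment, attrition and sessions completed have a related weakness: a significant result says that the three arms are not all alike, without saying which pair differs. The article nevertheless assigns the impact of gamification on enjoyment to such a test.

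At stake is the trial's central claim. If the comparison is not fixed in advance, the choice of contrast and time point is open after the data are seen. A reader of the results could also be left to judge gamification from whether each active arm separately differs from sham, which is not a test of their difference.

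**Working it through.** **Step 1. Set hypotheses beside analyses.**

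| Outcome | Gamified versus standard hypothesised? | Comparison named in Statistical Methods |
|---|---|---|
| Pain intensity, interference, anxiety, depression | Yes | Sham as reference |
| Attentional and interpretation bias | Yes | Sham as reference |
| Perceived improvement | Yes | Sham as reference |
| Task-related engagement | Yes | None |
| Interest and enjoyment | Yes | Three-arm analysis of variance |
| Sessions completed | Yes | Three-arm analysis of variance |
| Attrition | Yes | Log-rank across conditions |

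No row names gamified versus standard.

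**Step 2. Does a sham reference prevent the test?** No. Gamified minus standard is the difference of the two sham-referenced coefficients, b_G − b_S, with variance Var(b_G) + Var(b_S) − 2Cov(b_G, b_S). In a simulated data set (30 per arm, three time points, maximum likelihood), the sham-referenced fit gave 0.610 (SE 2.134). Refitting with standard as reference gave 0.610 (SE 2.134) and the same log-likelihood. The contrast is absent from the default coefficient table but available from the model, provided that the group and group-by-time terms are still in it. Choosing the most parsimonious model by AIC could remove them.

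**Step 3. Can the overall test answer the question?** Inputs: 30 per arm (the stated minimum), two-sided 5%, SD 1. The protocol gives no planning effect for this trial, so the effects are illustrative: 0.72 is its quoted effect of gamification on motivation or engagement, and 0.45 is the pain-interference effect quoted in Sample Size Estimation. The noncentrality of the F test is n × Σ(mean − grand mean)².

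- Means 0, 0.72, 0.72 (sham, standard, gamified; no gamification effect): 30 × (0.48² + 0.24² + 0.24²) = 10.37.
- Means 0, 0, 0.72 (effect entirely due to gamification): 30 × (0.24² + 0.24² + 0.48²) = 10.37.

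The F test therefore has the same power in these two opposite situations. Results from 20,000 simulated trials each:

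| True means | Overall test significant | Gamified versus standard significant |
|---|---|---|
| 0, 0.72, 0.72 | 81% | 5% |
| 0, 0, 0.72 | 81% | 79% |
| 0, 0.45, 0.90 | 88% | 41% |

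**Step 4. How often would separate sham comparisons mislead?** Suppose that both active arms have the same true effect d against sham, analysed as change scores. Then SE = √(2(1 − ρ) × 2/n), each z statistic has mean d/SE, and the two correlate 0.5 through the shared sham arm. The quantity is the probability that gamified is significantly better than sham while standard is not significant. Assumptions: n = 28 (40 less 30% dropout) to 40 per arm, and pre-post correlation ρ = 0.5 to 0.7, which the article does not give.

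For d = 0.45, n = 28, ρ = 0.5: SE = √(2 × 0.5 × 2/28) = 0.267, d/SE = 1.68, probability 16.0%. The other three combinations give 16.2% (28, 0.7), 16.6% (40, 0.5) and 13.3% (40, 0.7). Across effect sizes:

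| d versus sham, both active arms | Probability |
|---|---|
| 0 | about 2% |
| 0.2 | 7–12% |
| 0.45 | 13–17% |
| 0.8 | 0.4–9% |

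A direct two-sided 5% contrast would falsely favour gamified in 2.5% of trials whatever d is.

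**The case against.** A reader might infer that gamified versus standard is never tested, or that sham is the sole reference throughout. The text supports neither. The models are said to be built to test the hypotheses, and those include this comparison. The reference category is a parameterisation, and Step 2 shows that the contrast comes unchanged from the sham-referenced fit. The article calls sham a reference group without calling it the only one, and the task-engagement model names none. Pairwise follow-up after an analysis of variance or log-rank test is also a detail that a condensed article may leave to a fuller plan.

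A reader might likewise infer that the authors intend to claim a gamification effect whenever gamified differs from sham and standard does not. No section says so. The Step 4 probability depends on that conjectured inference, on an effect size the protocol does not plan for, and on assumed correlations. The quoted 0.45 is described as found in the intervention group, so using it as a difference from sham is itself an assumption. The figure also concerns the symptom scores and says nothing about the analyses of variance or the log-rank test.

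These points limit the wording and the numbers. They do not remove the gap. The article does more than stay silent: it names a reference group in three places and gives a three-arm overall test the task of measuring the impact of gamification. Those stated choices do not line up with the stated hypotheses.

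**Conclusion.** The concern holds as a specification gap. The comparison that answers the trial's main question is hypothesised for every outcome in the Step 1 table and specified in none of the analyses. The overall tests named for enjoyment, sessions completed and attrition cannot supply it. The mixed models can, if the contrast is stated and the needed terms are kept.

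The document comparison rests on no assumption. The 81% against 5% for the overall test assumes 30 per arm and effects of 0.72 SD. The misleading-pattern probability is an illustration only, running from about 0.4% to 17% over effects of 0 to 0.8 SD.

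Naming the contrast does not make it well powered. On an end-point SD scale with 30 per arm, power for gamified versus standard is about 12% at d = 0.2, 41% at 0.45 and 80% at 0.72, before any gain from baseline or repeated measures. The confidence interval will therefore matter more than the P value.

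**What to change.** Prespecify gamified minus standard, with 95% CI, as the key test of gamification:

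- **Symptoms and perceived improvement:** a linear contrast from the fitted model at posttraining and at 1 month.
- **Attentional and interpretation bias:** the same contrast at posttraining.
- **Task-related engagement:** a contrast across stated sessions.
- **Interest and enjoyment, sessions completed:** a planned contrast in each analysis of variance.
- **Attrition:** a pairwise log-rank test.

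Keep the group and group-by-time terms that the contrast needs in every model regardless of AIC, and confine AIC to the rest of the model. Keep standard versus sham as the test of ABMT efficacy, and report gamified versus sham as the effect of the whole package. State how the three pairwise comparisons are handled for multiplicity.

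The cost is about one sentence per analysis and a few more contrasts to report. No new data, visits or participants are needed.
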